### Rationale for Treatment Dose

Ketorolac is available at McMaster Children’s Hospital for off-label use in children for vigorous pain. The acceptable dose range is 0.25-1 mg/kg/dose every 6 hours (maximum 30 mg/dose) [27]. Onset of action is 30 minutes after IV administration and the maximum effect is achieved at 2 hours with a total duration of action up to 6 hours. Available population PK study data [28] from 3 studies on 64 children (intraoperative) showed a decrease in both central and peripheral volume of distribution over the first few years of life and clearance decreases from infancy to adolescence. A single dose of 0.5 mg/kg ketorolac (maximum dose 10-30 mg) every 6 hours achieved a half maximal effective concentration at or above the established 0.37 mg/ml. Most of our participants aged 6 years and older will weigh at least 20 kg (50^th^ percentile) and receive the maximum ceiling dose of 10 mg (group B1). Hence, including low-dose group B2 (0.25 mg/kg to a maximum of 30 mg) will allow us to test 2 low dosing strategies since we are changing only one intervention per arm: (1) a lower dose per kg (0.25 mg/kg) is noninferior to standard dose (0.5 mg/kg) and (2) a lower ceiling dose (10 mg) is noninferior to standard ceiling dose (30 mg) (see Multimedia Appendix 2).

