## Introduction

### Background

Ketorolac tromethamine is a well-known nonopioid intravenous (IV) analgesic commonly used in children and adults for vigorous pain [1-3]. It is a nonsteroidal anti-inflammatory drug (NSAID) that inhibits the synthesis of inflammatory endogenous substances such as prostaglandins and thromboxanes. Ketorolac has been shown to provide similar analgesia to opioids after outpatient surgical procedures associated with moderate pain, such as fractures, hernia repair, and tonsillectomy [1,4]. Ketorolac is commonly used in the Emergency Department (ED) for renal colic, abdominal pain, chest pain and migraine headaches [5]. However, such use in children is “off-label” as there is a paucity of methodologically sound controlled trials in children to inform optimal and safe dosing.

Previous pharmacological studies show that young children have up to 2- to 4-fold higher clearance and volume of distribution of ketorolac compared to adolescents and adults [6]. This suggests that younger children need a relatively higher dose per kilogram body weight than adults and the currently used 10-15 mg ceiling dose applied to adults may not achieve equivalent analgesia in children [7,8]. Emerging evidence, only applicable to adults, suggests that low-dose ketorolac (10 mg) is as effective as standard dose (30 mg) in acute pain management [5,9-11] with higher doses not conferring further benefit [12]. This has led to clinicians adopting the practice of a 10 mg maximum dose in children without rigorous pediatric evidence. For example, a 10 mg maximum dose in a 50 kg adolescent would equate to 0.2 mg/kg, in contrast to pediatric studies that used 0.5-1 mg/kg, a maximum of 20-30 mg [10,13-16]. In a local survey (February 2022) of our ED physicians, pediatric hospitalists, and surgeons, 10/31 (32%) respondents said that they would administer ketorolac (0.5 mg/kg) up to a maximum of 30 mg, 20/31 (65%) use ketorolac up to a maximum of 10 mg, and 1/31 (3%) did not know the best dose to give. Although the local monograph and order-sets recommend a maximum dose of 30 mg, our local variation in practice is not surprising and reflects clinical uncertainty regarding the optimal dose.

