### Interventions

To maintain blinding of bedside clinical staff, patients, and research staff, we will administer an active intervention (ketorolac) and 2 controls (identical normal saline placebo) to each patient at 3 differing doses.

1) Standard-dose group A: IV ketorolac 0.5 mg/kg to a maximum of 30 mg, IV normal saline placebo given at 0.25 mg/kg to a maximum of 30 mg, or IV normal saline placebo given at 0.5 mg/kg to a maximum of 10 mg.

2) Low-dose group B. Group B1: IV ketorolac 0.5 mg/kg to a maximum of 10 mg, IV normal saline placebo given at 0.25 mg/kg to a maximum of 30 mg, or IV normal saline placebo given at 0.5 mg/kg to a maximum of 30 mg. Group B2: IV ketorolac 0.25 mg/kg to a maximum of 30 mg, IV normal saline placebo given at 0.5 mg/kg to a maximum of 30 mg, or IV normal saline placebo given at 0.5 mg/kg to a maximum of 10 mg.

For rescue analgesic therapy, any participant can be given any other non-NSAID analgesic at the discretion of the treating physician at least 60 minutes after the trial medication is administered. To minimize overdosing or AEs, any other NSAIDs can be given 6 hours post-intervention.

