## Discussion

The KETODOSE trial addresses a critical evidence gap in determining optimal ketorolac dosing for common acute pain indications in the ED, where current practices have relied largely on adult data and expert opinion. Should our findings demonstrate that lower-dose regimens (0.25 mg/kg up to 30 mg and 0.5 mg/kg up to 10 mg) are noninferior to standard dosing, this would provide the first high-quality evidence to support dose de-escalation in children with acute pain. Such findings could validate the common, but unproven, practice of using a 10 mg ceiling dose in children. Moreover, this trial tests whether ceiling dose or per-kilogram dosing is the driver of analgesic effectiveness. If 0.5 mg/kg up to a maximum of 10 mg is found to be noninferior to the standard 0.5 mg/kg up to 30 mg regimen, yet superior to 0.25 mg/kg up to 30 mg by the MID, this would suggest that a higher per-kilogram dose combined with a lower ceiling dose may represent the optimal ketorolac strategy for children, balancing efficacy with reduced drug exposure.

In preparation for this trial, we conducted and published [48] a systematic review and meta-analysis of 4 databases and trial registries in early 2022 to identify any RCTs regarding ketorolac dosing. We identified four RCTs that included 392 adult participants. Studies compared standard dose ketorolac (30 mg) to either mid-dose ketorolac (15-20 mg) or low-dose ketorolac (10 mg). Most trials had small sample sizes and used a single dose of IV ketorolac [5,9,11], with the exception of one study that used intramuscular ketorolac.[33] All trials used the 100-mm visual analogue scale to measure their primary outcome pain level at 1 hour (3 trials) or 4 hours (1 trial) [11] postintervention. Four trials with 196 participants compared IV ketorolac 30 mg to 15-20 mg, with a nonsignificant mean difference of 1.03 mm (95% CI –2.45 to 4.5). Two trials with 116 participants compared ketorolac 30 mg to 10 mg and found a nonsignificant mean difference of 1.55 mm (95% CI –2.42 to 5.53) favoring the 30 mg dose. There was consistency across all trials and an *I*^2^ of 0%. This suggests that, for adults with acute pain, there is no clinically or statistically meaningful difference between lower doses of ketorolac and standard doses, and that an analgesic ceiling to ketorolac is reached at 10 mg in adults. However, there were no published pediatric trials or registered ongoing trials on trial registries.

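### The dose contrast between arms changes with weight and reverses between the two low-dose arms at 40 kg, so the planned whole-arm comparisons cannot show whether ceiling or per-kilogram dosing drives the effect

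*Protocol article*

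**What the plan says.** Interventions defines the three active regimens. Group A receives "IV ketorolac 0.5 mg/kg to a maximum of 30 mg", B1 receives "IV ketorolac 0.5 mg/kg to a maximum of 10 mg" and B2 receives "IV ketorolac 0.25 mg/kg to a maximum of 30 mg".

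Rationale for Treatment Dose states that "Most of our participants aged 6 years and older will weigh at least 20 kg" and so reach the B1 ceiling. It then justifies adding B2 on the ground that two separate questions can be tested, one on dose per kg and one on the ceiling, "since we are changing only one intervention per arm".

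The Discussion goes further. It says that "this trial tests whether ceiling dose or per-kilogram dosing is the driver of analgesic effectiveness". It adds that if B1 is noninferior to A and superior to B2, then "a higher per-kilogram dose combined with a lower ceiling dose may represent the optimal ketorolac strategy for children". The Secondary Hypothesis expects B1 to beat B2 by 2.0 vNRS points.

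The Background gives a worked example that bears on this: "a 10 mg maximum dose in a 50 kg adolescent would equate to 0.2 mg/kg".

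On analysis, section (A) of the Analysis Plan specifies whole-arm ANCOVA adjusted for baseline pain, both for B1-A and B2-A and for the conditional exploratory B1-B2 comparison. Planned Subgroups and Table 1 list condition, age (6-11 versus 12-17 years), gender, sex, and race and ethnicity. Weight is not among them.

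**The concern.** A capped mg/kg rule gives a dose that depends on weight, and here the three caps take effect at very different weights. The size of the B1-A and B2-A contrasts therefore varies from child to child, and for B1-B2 the direction varies too. An average over the arm answers which strategy did better in the children enrolled. It does not say whether a difference came from the cap or from the per-kg dose.

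What is at stake is the trial's interpretation. The Discussion ties a positive result to the 10 mg ceiling in children generally and to B1 being the higher per-kg option. For heavier children, whose dose the ceiling changes most, the second statement is the opposite of what the regimens deliver, and no planned analysis is defined on weight to show it.

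**Working it through.** **The plan's own figures.** The Background example reproduces: 10 mg / 50 kg = 0.2 mg/kg. The sample size also reproduces. With SD 1.5, margin 1.0, true difference 0.2, one-sided alpha 0.025 and 80% power (Sample Size Calculations), n = 2 × (1.96 + 0.842)² × 1.5² / (1.0 − 0.2)² = 55.2, so 56 per group by the normal approximation. With the noncentral t, power is 0.799 at 56 and 0.806 at 57, which gives the stated 57. Then 57 × 1.05 = 59.9, so 60. The point made here does not affect the sample size.

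**Delivered dose by weight (w, kg)**, from the regimens in Interventions:

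- A = min(0.5w, 30), cap reached at 60 kg
- B1 = min(0.5w, 10), cap reached at 20 kg
- B2 = min(0.25w, 30), cap reached at 120 kg

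| Weight (kg) | A (mg) | B1 (mg) | B2 (mg) | B1/A | B2/A | B1 − B2 (mg) | B1 (mg/kg) | B2 (mg/kg) |
|---|---|---|---|---|---|---|---|---|
| 20 | 10 | 10 | 5 | 1.00 | 0.50 | +5 | 0.50 | 0.25 |
| 30 | 15 | 10 | 7.5 | 0.67 | 0.50 | +2.5 | 0.33 | 0.25 |
| 40 | 20 | 10 | 10 | 0.50 | 0.50 | 0 | 0.25 | 0.25 |
| 50 | 25 | 10 | 12.5 | 0.40 | 0.50 | −2.5 | 0.20 | 0.25 |
| 60 | 30 | 10 | 15 | 0.33 | 0.50 | −5 | 0.167 | 0.25 |
| 80 | 30 | 10 | 20 | 0.33 | 0.67 | −10 | 0.125 | 0.25 |
| 120 | 30 | 10 | 30 | 0.33 | 1.00 | −20 | 0.083 | 0.25 |

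The crossovers are exact. B1 = A where 0.5w ≤ 10, so w ≤ 20 kg. B1 = B2 where 10 = 0.25w, so w = 40 kg. B2 is half of A up to 60 kg and rises to equal it at 120 kg. Above 20 kg, B1 delivers fewer mg/kg than A as well as meeting a lower ceiling, so the delivered doses do not isolate the ceiling.

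**B1 versus B2 pooled.** Suppose, for illustration, that the B1-B2 effect is +d below 40 kg and −d above it, and that a share g of children is above 40 kg. The pooled effect is (1 − g)d − gd = (1 − 2g)d. That is 0.6d, 0 and −0.6d for g = 20%, 50% and 80%. The shares are assumptions.

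**B1 versus A pooled.** Suppose a share f weighs 20 kg or less (no dose difference, so no loss) and every other child loses exactly the margin, 1.0. The pooled loss is 1.0 × (1 − f). With 60 per arm, SE = 1.5 × √(2/60) = 0.274, and P(declare noninferiority) = Φ((1.0 − pooled loss)/0.274 − 1.96):

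| f (assumed) | Pooled loss | P(noninferiority declared) |
|---|---|---|
| 0 | 1.0 | 2.5% |
| 10% | 0.9 | 5.5% |
| 20% | 0.8 | 10.9% |

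**The case against.** The strongest reply is that the primary question compares dosing strategies in children aged 6-17 as they would be used. Any capped regimen gives weight-dependent contrasts, and averaging over the enrolled mix is then the intended quantity. This stands: the pooled B1-A and B2-A tests are valid for that purpose. A reader might infer that the primary noninferiority tests are invalid, and the document does not support that.

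The sentence about changing one intervention per arm is also literally true of the nominal rules. From A to B1 only the cap changes, and from A to B2 only the mg/kg figure. The fault lies in the inference drawn from it.

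The B1-B2 comparison is exploratory in the Analysis Plan and runs only if both arms are noninferior, so no primary conclusion depends on it. Nor is the secondary hypothesis simply reversed: below 40 kg the dose order agrees with it.

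A reader might also expect a large risk of a false noninferiority claim. If the whole loss is placed above 40 kg, a 1.0-point loss there passes with probability 72%, 45% or 19% when 30%, 50% or 70% of children exceed 40 kg. Those figures assume no loss up to 40 kg, although A and B1 already differ twofold at that weight. Nothing in the document supports that step, so they are illustrations at most.

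Finally, the planned age split at 12 years is related to weight and gives some protection. It is justified by metabolism and not defined on weight, so it is only a partial proxy. Weight terms in a model may also be left to an analysis plan that is not shown. The list of five subgroups and the interpretive claims, however, are stated in this article.

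**Conclusion.** The point holds as a limit on interpretation. By the protocol's own regimens, the B1-A contrast runs from none at 20 kg or less to threefold from 60 kg, and the B1-B2 contrast changes sign at 40 kg. The trial can say whether each strategy is noninferior to standard in the weights it enrols. It cannot separate ceiling from per-kg dosing, and the description of B1 as the higher per-kg dose is false above 40 kg, as the Background's 50 kg example already implies (0.2 mg/kg against 0.25 mg/kg in B2).

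The dose arithmetic needs no assumption. The size of any dilution does, because no weight distribution or dose-response shape is given. If only children at or below 20 kg have no contrast, the effect on the B1-A error rate is modest (5.5% or 10.9% at assumed shares of 10% or 20%). It is smaller still if few children are that light, as the Rationale suggests.

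**What to change.** Before the group codes are revealed:

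1. Pre-specify, as supportive analyses, a treatment-by-weight interaction with weight as a continuous variable. Report model-based B1-A, B2-A and B1-B2 differences with 95% CIs across the weight range, including below and above 40 kg.
2. Reconcile the Background example, the Secondary Hypothesis, Interventions, Rationale for Treatment Dose and the Discussion, so that conclusions concern whole strategies and weight-specific contrasts and not which factor is the driver.

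A supportive B1-A noninferiority analysis restricted to children above 20 kg is optional. It will add little if nearly all participants exceed that weight.

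The cost is some analysis-plan wording and a few more model outputs, using a weight already needed to calculate the dose. The intervals will be wide at 60 per arm, so these results should be read as estimates and not as further tests. The primary analysis and sample size are unchanged. No change to any dose is proposed, and no view is taken on which regimen is right.

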### Randomization and Participant Allocation

The study’s research pharmacist at McMaster Children’s Hospital research pharmacy will create a simple computer-generated block randomization list using Robust Randomization App [29] (Center for Biostatistics, Icahn School of Medicine at Mount Sinai) with random varying permutated blocks of 3, 6, and 9 and a 1:1:1 allocation ratio. The research pharmacists will prepare consecutively numbered study drug vials according to the randomization schedule, with clear labels and dosing instructions in each kit. At least 3 study drug kits will be stored in the password-protected ED medication dispensing machines as per standard operating procedures and Division 5 Good Clinical Practice Health Canada Guidelines. Drug kits will be replenished as needed (at a minimum, weekly) by the research pharmacists. Only the research pharmacists will retain the randomization codes.

A log of all screened patients will be maintained. If patients are eligible, details of the study will be discussed with patients and their caregiver. Consent and assent will be obtained as per the Hamilton integrated Research Ethics Board (HiREB) guidelines and approved consenting procedures (see Multimedia Appendix 3 for consent forms). The clinical research assistant will collect baseline clinical variables and will complete the data collection forms. Elements of baseline pain severity (assessed by vNRS), type of pain, location of pain, duration of pain since onset, associated symptoms (eg, nausea, anorexia, vomiting, dysuria, fever, and pain with movement) will be collected. The Clinical Research Assistant will then pick the next consecutively numbered drug kit and enter the drug kit coded number into Research Electronic Data Capture (REDCap; Vanderbilt University). The research nurse will administer the study drugs to the patient (ketorolac and placebo normal saline) according to the dosing guidelines as an IV push over 5 minutes. Five minutes is a safe timeframe to administer IV ketorolac. This is consistent with the instructions on the clinical drug monograph at our hospital. Time 0 will be defined as the point at which administration of the study drug is completed.

### Methods to Protect from Bias

Our study drug kits will contain active ketorolac and normal saline placebo (labelled as ketorolac) with instructions on dosing as per the randomization schedule. Ketorolac is identical to a normal saline placebo in appearance, consistency, and smell. Vials will contain clear liquid ketorolac 30 mg/ml or normal saline placebo ketorolac 30 mg/ml. Vials will be stored in consecutively numbered study drug kits according to the randomization schedule generated by the McMaster Children’s Hospital research pharmacy. The double-dummy design will ensure blinding of the research nurse drawing up and administering the drug. Bedside physicians and nurses, participants, and their families, investigators, research nurses, and clinical research assistants will all be masked to prevent bias in trial procedures and outcome assessment. Once participants are randomized, we will restrict all other pharmacologic analgesic cointerventions except acetaminophen and rescue therapy. Unblinding will not be permitted under any circumstances, as all participants will receive ketorolac and knowledge of the specific dose would not alter clinical management. Other medications that may be part of the patient’s treatment plan, such as antiemetics, antibiotics, or antihistamines, can be coadministered. Because the primary outcome is based on a self-reported pain scale, the semistructured survey will be conducted only after outcome assessments are completed. Research assistants can complete the semistructured survey after the 6-hour outcome assessment or, if the patient is discharged, within 7 days by phone or electronically. The trial is registered on clinicaltrials.gov (NCT05641363) [30].

### Concomitant Medications

To decrease the confounding effects of other analgesics, we will exclude anyone who, before randomization, received any NSAIDs or opioids in the preceding 6 hours and 4 hours, respectively. We will not allow any other concomitant analgesics (except acetaminophen) administration during the study enrollment (from randomization-60 minutes postrescue therapy if it was required). Patients who have taken acetaminophen before randomization will be eligible to participate. Acetaminophen is widely available for use as an over-the-counter medication analgesic and is effective for mild pain but not for moderate or severe pain. Ketorolac should still be effective when given alongside acetaminophen and has a different mechanism of action. In addition, patients with migraine will be allowed to have coadministration of antiemetics such as metoclopramide or ondansetron. This should not affect our outcomes since all those participants will receive ketorolac (at differing doses) as the only analgesic. All cointerventions will be recorded.

### Duration of Treatment and Follow-Up

Ketorolac and a placebo can be given as an IV slow push over 5 minutes with or without a drug pump. Only a single dose will be administered as part of the trial. The effects on pain will be monitored by obtaining baseline pain scores with the vNRS and at times 30, 60, 90, 120 minutes, and at 6 hours if they are still in the hospital. At follow-up, ED and inpatient chart reviews will be completed to determine results of investigations, AEs, total doses of opioids administered in morphine equivalents/kg, all types of NSAIDs administered, dose and frequency for each and the final diagnosis assigned. The survey will be completed within 7 to 14 days once all clinical outcomes are completed (6 hours postintervention).

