**Inclusion criteria and justification**
Age 6 years to <18 years: the primary outcome measure (11-point vNRS) is validated for use in children ≥6 years, and no other evidence-based acute pain measure is recommended for younger children [23-25].Currently experiencing vigorous pain (self-reported pain score >4 using the vNRS at the time of enrollment; ketorolac is used to treat moderate to severe pain) [26].Patients seen in the ED or inpatient setting with acute pain ≤30 days in duration [5].Patient with an IV cannula in situ or ordered (to minimize additional pain or distress).

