#### Secondary Endpoints

Secondary endpoints include the following:

vNRS score at 30, 90, and 120 minutes as well as 6 hours post administration.Proportion of participants who achieve the 2-point vNRS MID pain score reduction at 60 and 120 minutes.Proportion of participants who change the severity of their baseline pain category at all time points (mild = 0 to 3, moderate = 4 to 6, severe ≥7 on the vNRS)[24].Time to effective analgesia (ie, time at which a vNRS <3 is achieved postintervention).Proportion of participants requiring any rescue analgesia in each trial arm.Total amount administered as measured by morphine equivalent mg/kg within 8 hours of intervention.

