### Analysis Plan

#### (A) Primary Objective Analysis Plan

Data will be described in terms of mean (SD) or 95% confidence limits for normally distributed data and frequency (percentage) in the case of categorical data. The primary endpoint is the difference between the mean reduction in pain scores between each of the low-dose groups (B1, B2) and the standard-dose group (A) 60 minutes post intervention. The primary analysis will include all participants randomized based on the intention to treat analysis and a sensitivity per-protocol analysis will also be performed. A priori, the primary analysis will be adjusted for baseline pain scores using the analysis of covariance (ANCOVA)*.* Generalized estimating equations will be used to examine the impact of baseline pain score on vNRS outcomes across the entire time frame. Noninferiority would be shown if the lower limit of the 95% CI for the between group (groups B1vs A or B2 vs A) differences in the primary endpoint is >1.0. If >5% [34] of our vNRS scores are missing within 120 minutes, we will use multiple imputation to create 5 datasets wherein any missing pain data will be imputed with the Markov chain Monte Carlo method. For secondary endpoints, we will describe those outcomes using descriptive statistics and perform a linear (continuous), logistic, or ordinal regression (categorical or ordinal). If both low-dose strategies are shown to be noninferior to standard dose, we will conduct an exploratory analysis to see if one low-dosing strategy is superior to the other (group B1 vs B2). This will be conducted using ANCOVA to adjust for baseline pain scores and superiority will be determined by a difference that is defined by the MID of 2.0 on the 11-point vNRS. All analyses will be conducted in a blinded fashion. The research pharmacist will provide the trial statistician with anonymized group allocation codes, without revealing the dosing strategies associated with each group. The group identities will remain blinded to the statistician until the first draft of the manuscript with results has been completed. All analyses will be done using SAS (version 9.4; SAS Inc).

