**Secondary outcomes**											
		**Efficacy**									
			Pain relief at all time points		Between group differences in pain score at all study time points at 30, 90 and120 minutes		Low dose will be noninferior to standard dose at all time points.		GEE^e^: adjusted for baseline pain scores		
			Pain relief by the MID		Proportion who achieves a 2-point vNRS reduction at 60 and 120 minutes		Low dose will be noninferior to standard dose ketorolac regimens in reducing pain by the 2-point MID^f^ on vNRS		Regression analysis		
			Pain category change		Proportion of participants who change their baseline pain category at all time points (mild 1 to 3, moderate 4 to 6, severe ≥7 on vNRS)		No difference between low dose and standard dose ketorolac in pain category change at all time points		Regression analysis		
			Time to achieve mild or no pain level		Time to effective analgesia as measured by the time when vNRS of <3 is achieved		No difference between all ketorolac dosing arms.		Cox regression analysis		
			Rescue analgesia		Proportion of participants requiring any additional analgesia in each trial arm		No difference between all ketorolac dosing arms		Regression analysis		
			Opioid sparring		Total amount of opioid administered within 8 hours of intervention		No difference between all ketorolac dosing arms		Regression analysis		

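### The 6-hour vNRS is listed as an unrestricted secondary endpoint but collected only from children still in hospital, so its between-arm comparison is open to selection bias

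*Protocol article*

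**What the plan says.** Secondary Endpoints lists "vNRS score at 30, 90, and 120 minutes as well as 6 hours post administration", with no restriction on who contributes a 6-hour score. Duration of Treatment and Follow-Up restricts it: pain is scored at baseline and through 120 minutes, "and at 6 hours if they are still in the hospital". Methods to Protect from Bias also treats 6 hours as an outcome assessment, and foresees that some children will have been discharged.

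For analysis, the Primary Objective Analysis Plan says that secondary endpoints will be described and that the team will "perform a linear (continuous), logistic, or ordinal regression (categorical or ordinal"). Its missing-data rule reads: "If >5% [34] of our vNRS scores are missing within 120 minutes, we will use multiple imputation to create 5 datasets". It states nothing for a 6-hour score missing because the child has gone home.

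Table 1 defines the pain-over-time outcome as "Between group differences in pain score at all study time points at 30, 90 and120 minutes", with the hypothesis "Low dose will be noninferior to standard dose at all time points". The Methods paragraph of the Abstract and Trial Day-to-Day Operations also stop at 120 minutes. A second endpoint, change of pain-severity category, is assessed at every time point, so whether it includes 6 hours is equally unclear.

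**The concern.** Randomization protects a comparison of all children allocated to each arm. It does not protect a comparison of those who happen to be present 6 hours later, because presence is settled after treatment and may depend on how well treatment worked. If relieved children tend to leave, each arm's 6-hour sample loses its responders and the arm means move together. In a trial that hypothesizes noninferiority over time, that movement looks like support for the lower doses.

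At stake is a reading that pain relief is sustained equally at 6 hours, resting on a selected and possibly small subset. The primary noninferiority conclusion, at 60 minutes, does not depend on this score.

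**Working it through.** **Inputs from the protocol (Sample Size Calculations):** SD 1.5, assumed true difference 0.2, margin 1.0, one-sided alpha 0.025, power 80%, 57 per group raised to 60.

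**Inputs not in the protocol (assumed):** the share still in hospital at 6 hours, how strongly pain drives staying, and the correlation between pain at the discharge decision and pain at 6 hours. Ranges are given below.

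**Step 1. The plan's own figure.** n per group = 2 × SD² × (z0.975 + z0.80)² / (margin − difference)² = 2 × 2.25 × (1.960 + 0.842)² / 0.8² = 55.2, so 56. With the noncentral t distribution, power is 0.799 at 56 and 0.806 at 57, so 57 is reproduced; 57 / 0.95 = 60. This figure is for the 60-minute endpoint. None is stated for 6 hours.

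**Step 2. Selection on pain.** Simulation, 1,000,000 children per arm, with a = 0 for standard dose and a = 1 for low dose (normal scores, not rounded or cut to 0–10):

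- pain at the discharge decision: Yd = 4 + δa + 1.5u
- pain at 6 hours: Y6 = 4 + δa + 1.5(ρu + √(1 − ρ²)e)
- log-odds of still being in hospital: c + b(Yd − 4)

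Here u and e are independent standard normal, δ is the true difference, b is the log-odds of staying per vNRS point, and c is −1.4 or 0. Observed 6-hour difference for a true δ = 1.0:

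| b | share present, standard / low (c = −1.4; c = 0) | ρ = 0.5 | ρ = 0.8 |
|---|---|---|---|
| 0 | 20% / 20%; 50% / 50% | 1.00 | 1.00 |
| 0.5 | 22% / 31%; 50% / 61% | 0.94–0.95 | 0.91 |
| 1 | 27% / 43%; 50% / 67% | 0.85–0.87 | 0.76–0.79 |
| 2 | 34% / 57%; 50% / 72% | 0.75–0.78 | 0.61–0.66 |

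For a true δ = 0.2, the observed difference is 0.12 to 0.20 when b is above 0, and stays at about 0.20 when b = 0.

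**Step 3. Arm also affects staying by another route** (for example adverse events or rescue). Add γa to the log-odds, with b = 1, ρ = 0.8, c = −0.7:

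| γ | true δ = 0 | true δ = 1.0 |
|---|---|---|
| −1 | +0.24 | 1.00 |
| +1 | −0.23 | 0.57 |

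With no true effect, selection alone can make the low dose look worse or better.

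**Step 4. Precision, ignoring bias.** Noninferiority power = Φ(0.8 / (1.5 × √(2/n)) − 1.96). At n = 60: 0.8 / 0.274 − 1.96 = 0.96, power 0.83. If 70%, 50%, 30% or 20% of 60 remain (42, 30, 18, 12 per arm), power is 0.69, 0.54, 0.36 or 0.26.

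**The case against.** The strongest case against is that no section says discharge depends on pain. The protocol enrols "Patients seen in the ED or inpatient setting with acute pain ≤30 days in duration", so diagnosis, work-up and admission also decide who is present at 6 hours. Step 2 gives no bias when staying is unrelated to pain, and step 3 shows that the direction can change. This stands. A reader might infer that the comparison is certainly biased toward no difference; the document supports only that it is open to bias, most likely in that direction.

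A reader might also infer that most of a margin-sized difference would vanish. That takes a hard cut-off. With true means 3.0 and 4.0, and scores seen only above 3, the observed difference is 0.42 to 0.44 (SD 2.0 to 1.5). But that model keeps every child above 3, discharges every other, and selects on a score not yet taken when the child leaves. It is an extreme case; graded selection gives the milder range.

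A reader might extend the point to 90 and 120 minutes, or conclude that GEE must be replaced. The document does not support either. The in-hospital condition is attached to 6 hours only, Trial Day-to-Day Operations schedules the earlier scores without it, and imputation covers that window once more than 5% are missing.

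Finally, the stakes are modest, and a missing-data rule for one secondary time point may sit in an analysis plan that is not shown. That is fair, but it does not remove the point. The collection rule is fixed here, discharged children have no 6-hour score under it, and the endpoint list does not carry the restriction.

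**Conclusion.** The point holds as a limited one. Followed as written, the plan compares arms at 6 hours in a post-randomization subset that the stated imputation rule does not reach. The contradiction between the endpoint list, the follow-up section and Table 1 needs no assumption.

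The size of any bias does rest on assumptions. With SD 1.5, log-odds of staying between 0.5 and 2 per point and correlation 0.5 to 0.8, a true 1.0 is seen as about 0.61 to 0.95. It is unchanged if staying is unrelated to pain, and the bias can reverse if the arm affects staying by another route. The 60-minute primary analysis is untouched. A correction is worthwhile because it costs little and prevents a selected subset from being read as evidence of noninferiority at 6 hours.

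**What to change.** Before unblinding:

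- Remove 6-hour vNRS from the between-arm efficacy comparisons, including the pain-category endpoint, whose time points should be stated as ending at 120 minutes.
- Report the 6-hour score descriptively among children still in hospital, with the number present in each arm beside it.
- Make no noninferiority claim at 6 hours.
- Align Duration of Treatment and Follow-Up, Secondary Endpoints, the Primary Objective Analysis Plan and Table 1. The analysis plan should say that the regression models, GEE and imputation apply to scores through 120 minutes.

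The cost is wording, and one secondary endpoint becomes descriptive. The survey contact is no substitute for the missing scores: it takes place within 7 days or at 7 to 14 days, depending on the section, while the vNRS asks about current pain. With 170 of 180 children enrolled by April 2025, new same-day calls could reach few participants.
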